### Trial Objectives

The primary objective of the CaRe-ECMO trial is to investigate the impact of cardiopulmonary rehabilitation combined with usual care on rate of ready for ECMO weaning at CaRe-ECMO day 7 (refers to 7 days after the CaRe-ECMO program initiation), when compared to usual care alone. Secondary objectives are to evaluate the effects of cardiopulmonary rehabilitation on rate of ECMO weaning, total length of ready for ECMO weaning, total length of ECMO weaning, rate of weaning of mechanical ventilation, total length of mechanical ventilation, all-cause mortality, rate of major post-ECMO complications, ICU length of stay (LOS), total hospital LOS, total cost for hospitalization, cerebral performance category (CPC), activities of daily living (ADL), and HRQoL.

### Ethics Statement

The CaRe-ECMO trial has been prospectively registered at the ClinicalTrials.gov (https://register.clinicaltrials.gov/): NCT05035797, 1 September, 2021. The trial protocol has been reviewed and approved by the Research Ethics Committee at the First Affiliated Hospital of Nanjing Medical University. In accordance with the Declaration of Helsinki of 1964 (revised in 2013), a written informed consent will be obtained from the legal guardians of all the enrolled patients (17).

### Trial Setting

The CaRe-ECMO trial will be mainly conducted in the Department of Emergency Medicine, the First Affiliated Hospital of Nanjing Medical University (a 3,700-bed primary referral hospital in Nanjing, Eastern China), who is capable to provide ECMO therapy for ~200 critical care patients annually. Clinicians from the Department of Emergency Medicine are required to have training certifications in ECMO therapy and at least 5-year therapeutic experience in management of critical care patients supported with ECMO. The Department of Rehabilitation Medicine will mainly be responsible for cardiopulmonary rehabilitation delivery. Clinicians from both the departments will collaborate on cardiopulmonary rehabilitation prescription. Therapists are required to have a certified degree in cardiopulmonary rehabilitation and at least 3-year therapeutic experience with critical care patients. The trial coordinating group will implement the CaRe-ECMO program guidelines and standard operation procedures (SOPs) for all the medical staffs via a kickoff meeting to be held in September 2021 (Nanjing, China).

### Eligibility and Withdrawal Criteria

The consolidated criteria for patient enrollment are those: (1) aged 18 years or older; (2) eligible for receiving ECMO (VV or VA) therapy; (3) with mechanical ventilation; (4) with stable condition and eligible for cardiopulmonary rehabilitation after 72 h of ECMO; (5) with no contraindications for cardiopulmonary rehabilitation; (6) not pregnant; (7) with a life expectancy of more than 3 days; (8) wean from ECMO therapy within the first 3 days before the initiation of the CaRe-ECMO program; (9) not use ECMO as a bridge to recovery or definitive treatment (e.g., lung transplantation or heart transplantation); (10) not enrolled in another trial previously; and (11) sign informed consent form by the guardian (18). According to previously published guidelines, the specific indications and contraindications for VV-ECMO and VA-ECMO are given in Tables 2, 3, respectively (19, 20).

**Table 2 T2:** Indications and contraindications for VV-ECMO.

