## Abstract

**Background:** Mortality of patients suffering from critical illness has been dramatically improved with advanced technological development of extracorporeal membrane oxygenation (ECMO) therapy. However, the majority of ECMO-supported patients failed to wean from ECMO therapy. As one of several options, cardiopulmonary rehabilitation serves as effective intervention in the improvement of cardiovascular and respiratory function in various major critical illness. Nonetheless, its role in facilitating ECMO weaning has not yet been explored. The purpose of this study is to investigate the effectiveness of cardiopulmonary rehabilitation on rate of ready for ECMO weaning in ECMO-supported patients (CaRe-ECMO).

**Methods:** The CaRe-ECMO trial is a randomized controlled, parallel group, clinical trial. This trial will be performed in a minimum number of 366 ECMO-supported eligible patients. Patients will be randomly assigned to either: (1) the CaRe-ECMO group, which will be treated with usual care including pharmacotherapy, non-pharmacotherapy, and specific nursing for ECMO therapy and the CaRe-ECMO program; or (2) the control group, which will receive usual care only. The CaRe-ECMO program consists of protocolized positioning, passive range of motion (PROM) training, neuromuscular electrical stimulation (NMES), surface electrical phrenic nerve stimulation (SEPNS), and pulmonary rehabilitation. The primary outcome of the CaRe-ECMO trial is the rate of ready for ECMO weaning at CaRe-ECMO day 7 (refers to 7 days after the CaRe-ECMO program initiation). Secondary outcomes include rate of ECMO and mechanical ventilation weaning, total length in day of ready for ECMO weaning, ECMO weaning and mechanical ventilation, all-cause mortality, rate of major post-ECMO complications, ECMO unit length of stay (LOS) and hospital LOS, total cost for hospitalization, cerebral performance category (CPC), activities of daily living (ADL), and health-related quality of life (HRQoL).

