Respiratory PNF techniques	Manual thoracic expansion and compression	Therapist- or device-assisted pulmonary rehabilitation techniques	20 min per session 1 session per day	1. Improve chest wall compliance 2. Increase lung volume 3. Reduce and avoid atelectasis
Airway clearance techniques	Manual flutter mucus clearance	Therapist-, nurse- or device-assisted airway clearance techniques	20 min per session 1 session per day	1. Assist airway clearance 2. Reduce post-ECMO pulmonary complications (e.g., infection)
	High-frequency chest wall oscillation			
	Endotracheal suctioning			

*PROM, passive range of motion; NMES, neuromuscular electrical stimulation; SEPNS, surface electrical phrenic nerve stimulation; ICU, intensive care unit; PNF, proprioceptive neuromuscular facilitation*.

After randomized treatment, the primary outcome will be assessed at the CaRe-ECMO day 7 after last cardiopulmonary rehabilitation session. All the patients who are not responded (e.g., failure in fulfilling the criteria of ready for ECMO weaning and need continuous ECMO support), regardless of trial assignment, will be provided with open-label treatment of cardiopulmonary rehabilitation. Corresponding secondary outcomes will be assessed at the open-label stage according to the preplanned schedule.

Detailed procedure of the CaRe-ECMO program is shown in Figure 3.

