### Outcome Measures

#### Primary Outcome

The primary outcome of the CaRe-ECMO trial is the rate of ready for ECMO weaning at CaRe-ECMO day 7. It means that rate of ready for ECMO weaning will be calculated 7 days after cardiopulmonary rehabilitation delivery. Checklists to define ready for ECMO weaning (hereafter called ready for ECMO weaning checklists), either for VV-ECMO or VA-ECMO, have been prepared according to literature review and shown in Tables 5, 6 (20, 28). A fixed medical staff will be responsible for checkouts of listed items daily. Eligible patients defined as ready for ECMO weaning reveal the fulfillment of all the items in the checklists. Date of ready for ECMO weaning will be recorded and the rate of ready for ECMO weaning at CaRe-ECMO day 7 will be calculated.

**Table 5 T5:** Ready for VV-ECMO weaning checklist.

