**Ready for VA-ECMO weaning checklist**	
Move forward to the nest step when the former step is fulfilled, should all of the steps be fulfilled indicating the patient is ready for ECMO weaning	
Step 1	The etiology of cardiac failure must be compatible with myocardial recovery
Step 2	Pulmonary function should not be severely impaired: If FiO_2_ ≤ 50%, PEEP < 10 cmH_2_O, PIP < 30 cmH_2_O, PaO_2_ > 70 mmHg, PaO_2_/FiO_2_ > 200 mmHg, PaCO_2_ < 45 mmHg, pH 7.35–7.45, no pulmonary edema in X-ray/CT scanning, then move to the next step
Step 3	Hemodynamic and cardiac functional assessment: If MAP > 70 mmHg and PPD > 30 mmHg for 24 h, the heart rate increases over 20% of the baseline following the reduction of ECMO flow, VIS of <10, LVEF of more than 40%, aortic VTI of more than 10 cm/s, decreasing trend of cTnT and BNP values, CVP < 12 cmH_2_O, lactate < 2 mmol/L, SvO_2_ > 70%, with improved function of other damaged organs, then move to the next step
Step 4	The patient must tolerate a full weaning trial: Increase ACT to 200 s, then gradually reduce ECMO flow to 66% for 15 min, and then to 33% of its baseline value for 15 min, and finally a minimum of 1–1.5 L/min for 15 min. During the weaning trial, monitoring the patient to maintain parameters mentioned in Step 3
Step 5	The patient is ready for VA-ECMO weaning

*VA-ECMO, venoarterial extracorporeal membrane oxygenation; FiO_2_, fraction of inspired oxygen; PEEP, positive end-expiratory pressure; PIP, peak inspiratory pressure; PaO_2_, partial pressure of arterial oxygen; PaCO_2_, partial pressure of arterial carbon dioxide; MAP, mean arterial pressure; PPD, pulse pressure difference; VIS, vasoactive-inotrope score; VTI, velocity time integral; cTnT, cardiac troponin T; CVP, central venous pressure; SvO_2_, mixed venous oxygen saturation; ACT, activated clotting time*.

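### Enrolment criterion 8 as written requires the patient to have been weaned from ECMO before the programme starts, which contradicts criterion 4 and the primary outcome; criterion 9 also needs reconciling with the weaning checklists

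*Protocol article*

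**What the plan says.** The protocol article gives one eligibility list of eleven items, introduced with the words "The consolidated criteria for patient enrollment are those". Table 1 refers to this section, with Tables 2 and 3, for both inclusion and exclusion criteria, so the article has no separate exclusion list.

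Three items matter here:

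- Item 4: "4) with stable condition and eligible for cardiopulmonary rehabilitation after 72 h of ECMO".
- Item 8: "8) wean from ECMO therapy within the first 3 days before the initiation of the CaRe-ECMO program".
- Item 9: "9) not use ECMO as a bridge to recovery or definitive treatment (e.g., lung transplantation or heart transplantation".

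The Abstract describes the trial population as on ECMO: "This trial will be performed in a minimum number of 366 ECMO-supported eligible patients". The Primary Outcome section states: "The primary outcome of the CaRe-ECMO trial is the rate of ready for ECMO weaning at CaRe-ECMO day 7". For patients on VA-ECMO, step 1 of the readiness checklist (Table 6) is "The etiology of cardiac failure must be compatible with myocardial recovery".

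**The concern.** Eligibility criteria are operative rules. They decide who is randomised and to whom the result applies. Item 8, taken at its word, admits only patients whose ECMO has already ended. Such a patient has no support left to be weaned from and cannot contribute a primary event.

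Item 9 raises a lesser question. It excludes one purpose of ECMO, bridging to recovery, while the endpoint is built on recovery. Two screeners could decide differently on the same patient.

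**Working it through.** No figure in the plan belongs to this point, so the check sets the sections side by side.

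**Item 8: is it an inclusion or an exclusion condition?** The list mixes both kinds, but the other exclusion-type items are marked. Items 5 (contraindications to rehabilitation), 6 (pregnancy), 9 (purpose of ECMO) and 10 (earlier trial enrolment) each contain an explicit negative. Item 8 contains none. By the list's own convention it is a condition to be met.

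**Item 8: what does the time window mean?** The phrase allows two readings.

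1. The first 3 days of ECMO. Three days are 3 × 24 = 72 h. Item 8 then asks for weaning within 72 h and item 4 asks for eligibility after 72 h of ECMO, so almost nobody could meet both.
2. The 3 days just before the programme. A patient could then have had more than 72 h of ECMO, but would still be off it when the programme begins.

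Under either reading the patient is off ECMO at the start. The document does not discuss a patient who is weaned and then put back on support.

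**Item 8 against the rest of the article:**

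| Section | What it presupposes at programme start or later |
|---|---|
| Enrollment, Randomization, and Allocation | Patients being enrolled are receiving ECMO |
| Interventions, CaRe-ECMO Group | Daily screening checks that ECMO flow and cannula position are stable |
| Primary Outcome | The patient can still become ready for weaning by day 7 |
| Table 5, step 4 | The circuit's oxygen supply is disconnected while flow is kept up |
| Table 6, step 4 | ECMO flow is lowered in stages |
| Interventions, paragraph after Table 4 | Non-responders show "failure in fulfilling the criteria of ready for ECMO weaning and need continuous ECMO support" |
| Discussion | Median time to ECMO weaning is about 7 to 9 days |

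Every row needs a running circuit or a patient who stays on ECMO beyond day 3. None is compatible with item 8 as written, and no visible text corrects it.

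**Item 9 against the checklists and rationale.** Item 9 excludes two uses of ECMO, as a bridge to recovery and as a bridge to definitive treatment. The examples in brackets are both transplantation, which illustrates only the second. On the other side:

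- Table 6 step 1 requires a cause of cardiac failure that is compatible with recovery.
- Table 5 step 1 requires the underlying disease to be controlled or improved.
- The Introduction presents ECMO as buying time for the body, and rehabilitation as a means of speeding recovery after the first 72 h.

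The endpoint and the rationale are therefore about recovery, while item 9 names recovery as an excluded purpose. The article does not define bridge to recovery in a way that would settle this.

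**The case against.** The strongest reply is that item 8 is a slip with only one workable correction. Item 4 stands in the same sentence, the Abstract speaks of ECMO-supported patients, and the rehabilitation screen cannot be run without a circuit. A careful screener would read the missing negative into the item. This stands, and it limits the practical danger. It does not make the text right: the criterion is stated in full, it is wrong as stated, and whoever applies it must first notice that it cannot be meant.

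For item 9, the reply is that the purpose for which ECMO is used differs from the cause of the organ failure. That also stands. A reader might infer that every VA patient with a recoverable cause is shut out, and that those are the only VA patients who could reach the endpoint. Neither follows, because a cause compatible with recovery is not the same as ECMO designated as a bridge to recovery. The bracketed examples also suggest that a narrower exclusion was meant.

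A reader might further infer that the 30% and 45% planning rates and the target of 366 no longer apply. That would rest wholly on the literal reading of item 8. The Sample Size Calculation section takes its rate from retrospective data and literature, and nothing shows that those patients were selected with the faulty wording. Nor can it be said that the registry entry needs correcting, since that record is not available here. Figures 1 and 2 are not shown either, and they can neither confirm nor rebut the point.

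**Conclusion.** Item 8 is wrong as written and must be corrected. It is an internal contradiction in an operative rule, most probably through a lost negation. Applied literally, 0% of enrolled patients would be at risk of the primary event (leaving aside anyone returned to ECMO after weaning). Applied in the sense that the rest of the article points to, the trial population is unaffected. The document gives no basis for a figure between these two, so no loss of power is claimed.

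Item 9 is a secondary point. Its wording is unclear and in tension with Table 5 step 1, Table 6 step 1 and the Introduction, but it is not shown to remove the endpoint population. Which bridge uses should be excluded is for the trial team to decide.

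The conclusion assumes that the list in the article is the one that screeners will use, and that the figures not shown do not restate these criteria differently.

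**What to change.** Before the first enrolment:

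1. Restate item 8 as a negative condition: the patient has not been weaned from ECMO in the first 3 days, and is still ECMO-supported when the CaRe-ECMO programme starts. This brings it into line with item 4 and the primary outcome. State that the 3 days are counted from the start of ECMO, if that is what is meant.
2. Reconcile item 9 with Table 5 step 1, Table 6 step 1 and the Introduction, and state explicitly which bridge uses of ECMO are excluded.

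Table 1 gives recruitment as not yet started, so the cost is a correction of two list items. No patients are added, and neither the endpoint nor the planned analysis changes.

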**Indications for VV-ECMO (one or more of the following)**
1. Hypoxemic respiratory failure (PaO_2_/FiO_2_ < 80 mmHg), after optimal medical management (FiO_2_ > 80%)
2. pH < 7.25 with PaCO_2_ ≥ 60 mmHg for more than 6 h, despite optimal conventional mechanical ventilation (respiratory rate of 35 bpm and P_plat_ ≤ 30 cmH_2_O)
3. Airway obstruction, unable to establish advanced airways
**Contraindications for VV-ECMO**
1. Irreversible non-cardiac organ failure limiting survival (e.g., severe anoxic brain injury or metastatic cancer)
2. Irreversible and incapacitating central nervous system pathology
3. Irreversible and incapacitating cardiovascular system pathology
4. Systemic bleeding
5. Mechanical ventilation for more than 7 days with P_plat_ > 30 cmH_2_O and FiO_2_ > 90%
6. Limited vascular access (severe peripheral arterial disease, extreme obesity, amputated limbs, among others)
7. Older age (increasing risk of death with increasing age)

*VV-ECMO, venovenous extracorporeal membrane oxygenation; PaO_2_, partial pressure of arterial oxygen; FiO_2_, fraction of inspired oxygen; PaCO_2_, partial pressure of arterial carbon dioxide; P_plat_, plateau pressure*.

**Table 3 T3:** Indications and contraindications for VA-ECMO.

**Indications for VA-ECMO (one or more of the following)**
1. Rapidly deteriorating or severe cardiogenic shock (cardiac Index < 2.2 L/min/m^2^ with ^*^ VIS > 40) with LVEF < 35%
2. Rapidly deteriorating or severe cardiogenic shock (cardiac Index < 2.2 L/min/m^2^ with ^*^ VIS > 40) with LVEF of 35–55%, and severe mitral regurgitation or aortic stenosis
3. Two consecutive lactate values ≥4 mmol/L (with at least 30 min interval between sampling), with non-decreasing trend on steady dose of inotropes and/or vasopressors
4. Witnessed cardiopulmonary resuscitation for more than 10 min or intermittent ROSC but unable to maintain
**Contraindications for VA-ECMO**
1. Irreversible non-cardiac organ failure limiting survival (e.g., severe anoxic brain injury or metastatic cancer)
2. Irreversible and incapacitating central nervous system pathology
3. Irreversible and incapacitating cardiovascular system pathology
4. Systemic bleeding
5. Aortic dissection
6. Limited vascular access (severe peripheral arterial disease, extreme obesity, amputated limbs, among others)
7. Older age (increasing risk of death with increasing age)

*VA-ECMO, venoarterial extracorporeal membrane oxygenation; LVEF, left ventricular ejection fraction; SvO_2_, mixed venous oxygen saturation; ROSC, return of spontaneous circulation; VAD, ventricular assist device*.

* *Vasoactive-inotrope score (VIS): (Epinephrine dose + Norepinephrine dose) μg/kg/min × 100 + (Dopamine dose + Dobutamine dose) μg/kg/min*.

Patients will be withdrawn from the trial if: (1) the guardian makes such a request with no reasons; (2) the patient develops adverse events due to cardiopulmonary rehabilitation (e.g., rib fracture, limb fracture); and (3) the patient develops ECMO-related complications (e.g., bleeding, thromboembolism, severe infection) and is ever unsuitable for participating in the trial according to the point of view by clinicians.

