#### Control Group

No additional rehabilitation intervention, except usual care and ECMO therapy, will be provided to patients in the control group.

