#### Secondary Outcomes

Secondary outcomes are listed and elaborated as follows:

1) Rate of ECMO weaning will be calculated according to date of ECMO weaning fulfilled.2) Total length of ready for ECMO weaning refers to exact length in day till patients fulfill all the criteria of ready for ECMO weaning according to daily checkout records (14).3) Total length of ECMO weaning refers to exact length in day for patients treated with ECMO therapy (29).4) Rate of mechanical ventilation weaning will be calculated according to date of mechanical ventilation weaning fulfilled. Daily screening of mechanical ventilation weaning will be strictly performed with checklist shown in Table 7 according to the American Thoracic Society and the American College of Chest Physicians Clinical Practice Guideline (30).5) Total length of mechanical ventilation refers to exact length in day for patients treated with mechanical ventilation.6) All-cause mortality is defined as rate of death due to any causes and will be calculated according to date of death (31).7) Rate of major post-ECMO complications refers to rate of complications occurred after ECMO including but not limited to ECMO-related complications (e.g., thromboembolism), mechanical ventilation-related complications (e.g., pneumonia), newly developed myocardial infarction, acute kidney injury, neurologic events (e.g., stroke, seizures), and multiple organ failure (32). Information of major post-ECMO complications will be collected in the Complication Recording Sheet (Table 8).8) Diaphragmatic thickness and mobility refer to ultrasound-guided evaluation of diaphragmatic thickness and mobility under M-mode (33).9) Extracorporeal membrane oxygenation unit LOS accounts for length in day for stay of patients in the ICU unit.10) Total hospital LOS accounts for total hospital LOS in day for stay of patients in both the ECMO unit and other departments.11) Total cost for hospitalization will be calculated by addition of the cost of all the units and department admission.12) Cerebral performance category will be recorded, for those successfully weaning of ECMO, to reflect post-ECMO neurological status (34).13) Activities of daily living will be evaluated, for those successfully weaning of ECMO, with Katz Index (35).14) Health-related quality of life will be measured, for those successfully weaning of ECMO, with SF-12 (36).

**Table 7 T7:** Mechanical ventilation weaning checklist.

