### Sample Size Calculation

We considered the rate of ready for ECMO weaning being conservatively 50% higher in the CaRe-ECMO group than in the control group at CaRe-ECMO day 7 as a clinically meaningful effect, implying a hazard ratio (HR) of 0.5. Accordingly, we performed sample size calculation for the Cox proportional hazards model with an alpha error of 5% and a power of 80%, effect size of HR = 0.5, and overall event (ready for weaning) probability of 30% at CaRe-ECMO day 7 (increases from 30 to 45%) according to our retrospective data analysis and literature review (38). The needed sample size was estimated as *n* = 348, i.e., 174 per group. Due to the relative short observational period and the real-world situation (e.g., patients treated with ECMO therapy generally will not discharge till stable or death), accounting for 5% attrition according to their failing for fulfill of daily eligibility screening for cardiopulmonary rehabilitation during the therapeutic period, the target sample size is set at 366 (183 per group).

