### Statistical Methods

The demographic and clinical characteristics collected at randomization will be presented as means with SDs or medians with interquartile ranges for continuous variables and as percentages for categorical variables, as appropriate.

For all the outcomes, we will estimate differences in effect size between the groups on both the intention-to-treat (ITT) and per protocol (PP) basis (39). Categorical variables will be compared with the chi-square or Fisher's exact tests and continuous variables will be compared with the Student's *t*-test or the Wilcoxon signed-rank test, as appropriate. The time effect of day the time-to-event outcomes identified (e.g., rate of ready for ECMO weaning, rate of ECMO weaning, rate of mechanical ventilation weaning, all-cause mortality, and rate of major post-ECMO complications) between the groups will be estimated with the Cox proportional hazards regression analysis and graphically illustrated using the Kaplan–Meier methods until CaRe-ECMO days 7, 14, 30, and 90, respectively (40). Variables, including total length of ready for ECMO weaning, total length of ECMO weaning, total length of mechanical ventilation, ECMO unit LOS, and total hospital LOS, will be treated with time-to-event data and will be analyzed with mixed-effects ordered logistic regression (41). Secondary outcomes with normal and non-normal distributions, including CPC, ADL, HRQoL, and diaphragmatic thickness and mobility, will be estimated for group differences with mixed-effects linear regression (41).

Considering that part of patients will definitely not reach the primary endpoint, i.e., ready for ECMO weaning at CaRe-ECMO day 7 for sensitivity purpose, we will assess the heterogeneity of the treatment effect on primary outcome and secondary outcomes in pre-specified subgroups of interest as per baseline data to be collected at randomization (e.g., age, gender, main diagnosis, comorbidities, the APACHE II score, ECMO mode, length since mechanical ventilation) by using exploratory *post-hoc* sensitivity adjusted analyses for any corresponding statistical methods mentioned above.

Interim analysis will be scheduled halfway through enrollment to check that there are no serious issues with respect to sample handling or data collection.

All the analyses will be conducted at a two-sided alpha level of 5% and will be performed using the Stata version 16 (StataCorp, College Station, Texas, USA) or other software, as appropriate.

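### Withdrawal from the trial for rehabilitation adverse events, and failed rehabilitation screening counted as attrition, are not reconciled with the planned ITT analysis and put it at risk

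*Protocol article*

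**What the plan says.** **Withdrawal.** Under Eligibility and Withdrawal Criteria (text after Table 3), the list opens "Patients will be withdrawn from the trial if" and gives three reasons. The first is the guardian's request. The second is "2) the patient develops adverse events due to cardiopulmonary rehabilitation (e.g., rib fracture, limb fracture"). The third is that "the patient develops ECMO-related complications (e.g., bleeding, thromboembolism, severe infection) and is ever unsuitable for participating in the trial", in the clinicians' view.

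**Control arm.** The Control Group section states "No additional rehabilitation intervention, except usual care and ECMO therapy, will be provided to patients in the control group".

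**Adverse events during rehabilitation.** The CaRe-ECMO Group section has a different consequence: the session is discontinued, and the reason and length of therapy are recorded. It does not mention leaving the trial. The daily eligibility screen for rehabilitation is described only in that section.

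**Attrition.** The Sample Size Calculation raises 348 to 366, "accounting for 5% attrition according to their failing for fulfill of daily eligibility screening for cardiopulmonary rehabilitation during the therapeutic period".

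**Outcomes and analysis.** Secondary outcome 7 is the "rate of complications occurred after ECMO including but not limited to ECMO-related complications (e.g., thromboembolism") and further groups of events. Statistical Methods plans to estimate effects for all outcomes "on both the intention-to-treat (ITT) and per protocol (PP) basis" and does not say which basis is primary. Data Collection takes readiness, weaning, death and complications from daily evaluations in the medical records.

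**The concern.** An ITT comparison needs every randomised patient's outcome, counted in the allocated arm. Three stated rules pull against this.

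- Reason 2 ends trial participation because of an event that, during the randomised period, only one arm can have.
- Reason 3 can end participation when an event of a secondary outcome occurs, on a judgement by clinicians. The Blinding section says only that its measures may help to blind them.
- Failed screening is treated as attrition. A patient who misses rehabilitation because of instability is still in hospital and still has a day-7 readiness status. Allowing for that patient as lost fits an analysis that drops the patient, not ITT.

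If the patients removed differ in prognosis from those who stay, and removal is concentrated in one arm, the primary comparison is no longer protected by randomisation. Because ITT and PP have equal standing in the text, a result that leaves these patients out could be reported as the main one.

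**Working it through.** **1. The plan's own figure.** 348 × 1.05 = 365.4, rounded up to 366; per arm 174 × 1.05 = 182.7, rounded up to 183. Dividing instead, 348 / 0.95 = 366.3, gives 367. The inflation therefore reproduces, and the allowance is 366 − 348 = 18 patients. (Whether 348 follows from the stated Cox calculation is a separate matter and is not used here.)

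**2. Where each rule can act in the first 7 days.**

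| Rule | CaRe-ECMO | Control |
|---|---|---|
| Reason 2, rehabilitation adverse event | yes | no, as no rehabilitation is given |
| Reason 3, ECMO complication and judged unsuitable | yes | yes |
| Failed daily rehabilitation screen | yes | screen not described |

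After day 7, non-responders in either arm are offered open-label rehabilitation, so reason 2 could then reach controls.

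**3. Possible effect on the primary comparison.**

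Inputs from the protocol: 183 per arm, 30% ready by day 7, two-sided alpha 5%.

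Assumptions not in the protocol: no true effect; a fraction w of the CaRe-ECMO arm removed and no controls removed; a fraction r of those removed would have become ready; a pooled two-proportion z-test on day-7 status in place of the Cox model.

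Observed CaRe-ECMO rate: p2 = (0.30 − w·r) / (1 − w).

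Rejection probability: 1 − Φ((1.96·s0 − d)/s1) + Φ((−1.96·s0 − d)/s1), where d = p2 − 0.30, s0 is the pooled standard error and s1 the unpooled one.

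Example, w = 10% and r = 0:
- p2 = 0.30/0.90 = 0.333, with 183 against 164.7 patients.
- The pooled rate is 0.3158, s0 = 0.0499, s1 = 0.0500 and d = 0.0333.
- The two tails are 0.098 and 0.004, together 10.3%.

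| w | p2, r = 0 | Error, r = 0 | p2, r = 15% | Error, r = 15% |
|---|---|---|---|---|
| 5% | 31.6% | 6.2% | 30.8% | 5.3% |
| 10% | 33.3% | 10.3% | 31.7% | 6.3% |
| 15% | 35.3% | 18.0% | 32.6% | 8.2% |

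Simulation with 400,000 trials per cell agrees within 0.2 percentage points. With r = 30%, the same as controls, the error stays at 5.0%.

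Only the 5% is a figure from the protocol, and there it refers to screening failure. If all 18 allowance patients came from the CaRe-ECMO arm, that would be 18/183 = 9.8% of it, close to the 10% row. This is an interpretation, since the protocol spreads the allowance over both groups.

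**4. Cost of keeping everyone.** Power of the same test for 30% against 45% at 183 per arm is 84.5%. If 5% of the CaRe-ECMO arm receive no rehabilitation but are analysed as randomised:
- They fare as controls: 0.95 × 45% + 0.05 × 30% = 44.25%, power 80.8%.
- None becomes ready: 0.95 × 45% = 42.75%, power 71.9%.

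At 9.8% untreated, the same two cases give arm rates of 43.5% and 40.6%, with power 76.7% and 56.3%.

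**The case against.** Four points can fairly be made on the other side.

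**ITT is planned and can be done.** A reader might infer from the withdrawal rules that it cannot be carried out. The documents do not support that. Statistical Methods names ITT, outcomes come from daily records, and the sample size section says patients generally stay in hospital until stable or dead. Nothing says that withdrawn patients' data are discarded. This stands. What remains is that the withdrawal rule, followed as written, ends trial participation, and no passage brings it into line with ITT. That is a stated rule in conflict with the analysis, not detail left to a fuller document.

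**One-sided loss of poor-prognosis patients is not shown.** Reason 3, the ground most plausibly tied to prognosis, covers both arms and also needs the judgement that the patient "is ever unsuitable for participating in the trial according to the point of view by clinicians". Reason 2 gives fractures as examples, and the documents do not link these to readiness for weaning. This stands too, so the direction of any bias is an assumption.

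**Harms are not simply hidden.** A reader might infer that they are. A complication that triggers withdrawal has already occurred and has a dated place on the Complication Recording Sheet; reasons for stopping rehabilitation are recorded; the monitoring section provides a safety review. Only events after withdrawal are at risk of being missed.

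**Failed screening is not a listed withdrawal reason.** The 5% could be read as protecting the PP analysis. That reading is possible, but the text calls it attrition and does not tie it to PP.

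**Conclusion.** The point holds as a conflict between stated rules. Leaving the trial for a rehabilitation adverse event, stopping only the session for such an event, counting failed screening as attrition, and analysing by ITT do not fit together, and neither ITT nor PP is named primary. This threatens the ITT comparison without making it impossible.

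The effect on two-sided error ranges from none, if removed patients resemble those who stay, to roughly 18% at 15% removed with none otherwise becoming ready. At the protocol's only figure, 5%, it is about 5% to 6%. These numbers rest on removal from the CaRe-ECMO arm alone and on assumed readiness among those removed, neither of which the documents give.

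The matter should be settled before enrolment, because it governs who is counted in the primary comparison.

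**What to change.** 1. Reconcile the Eligibility and Withdrawal Criteria, the CaRe-ECMO Group section and Statistical Methods. State that, whatever clinical rule stops rehabilitation, patients stopped for reason 2 or 3, or failing the daily screen, stay in the trial, have all outcomes collected to day 90, and are analysed in the arm to which they were randomised. Only withdrawal of consent ends data collection.
2. Name ITT as the primary analysis and PP as supportive.
3. In the Sample Size Calculation, restate the 5% as treatment non-receipt retained in ITT, and give power as a range: about 72% to 81% at 183 per arm for 30% against 45%, by the day-7 proportion test used above.

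No rule on when rehabilitation is stopped is proposed here.

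The cost is some protocol wording and continued follow-up of a small number of patients, for the inpatient outcomes from records already kept. The real downside is dilution of the effect. It is modest if untreated patients fare as controls. If none of them becomes ready, power falls clearly below 80%, and the sponsor should know this before fixing the target.
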